## Abstract

**Background:**

Metastatic spine tumor surgery (MSTS) is often complex and extensive leading to significant blood loss. Allogeneic blood transfusion (ABT) is the mainstay of blood replenishment but with immune-mediated postoperative complications. Alternative blood management techniques (salvaged blood transfusion [SBT]) allow us to overcome such complications. Despite widespread use of intraoperative cell salvage (IOCS) in oncological and nononcological surgical procedures, surgeons remain reluctant to use IOCS in MSTS.

**Objective:**

This study aims to analyze safety of IOCS-leukocyte depletion filter (LDF)–processed blood transfusion for patients undergoing MSTS by assessing clinical outcomes—disease progression: tumor progression and overall survival. This study evaluates whether reinfusion of IOCS-LDF–processed blood reduces ABT rates in patients undergoing MSTS by sorting patients undergoing MSTS who require ABT into patients who consent to receive or not receive SBT.

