#### Secondary Objectives

The secondary objectives of the study are to investigate whether reinfusion of IOCS-LDF–processed blood can reduce ABT rates in patients undergoing MSTS. We will also compare the length of stay and overall complication rate of patients who receive salvaged blood and those who receive ABT or no blood transfusion (NBT).

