## Methods

### Recruitment

This study aims to recruit a minimum of 90 patients of whom 30 will receive SBT (with or with no allogeneic blood), 30 will undergo ABT, and the remaining 30 will have NBT. From our experience of treating patients with tumor, there are likely to be very few patients who receive only SBT. The majority of patients receiving SBT are likely to receive both SBT and ABT in various proportions. SBT and ABT form the 2 experimental arms, whereas patients with NBT form the control cohort. We will compare the number of patients receiving only SBT with those receiving ABT, if the sample sizes are sufficient.

Patients will be selected from specialist outpatient spine clinics or inpatient wards. These patients may be referred from an inpatient medical oncology team for management, especially in the setting of MSD with cord compression resulting in symptoms such as pain or neurology. A thorough examination of clinical history, physical examination, and review of imaging will be done, and appropriate patient management options will be discussed by the attending orthopedic surgeon. During the enrollment period, whenever a spine surgeon has obtained surgical consent for MSTS in patients with MSD, the principal investigator (NK) will be informed either by a telephone call or by text messaging.

The *research assistant* who is on-site at the National University Hospital during office hours or any member of the research team who is available will interview the patient. During this interview, the interviewer will confirm whether the inclusion criteria are fully met. The study will be explained to suitable subjects, including the advantages as well as possible intra- and postoperative risks of the reinfusion of salvaged blood. A copy of the *patient information sheet and consent form* will be provided to the patient, detailing the recruitment procedures, our objectives, hypotheses, and background information, and any queries will be addressed. Subsequently, written informed consent will be obtained from the patient.

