Blood transfusion details will be collected from anesthetists immediately after the operation. Depending on the type of blood transfusion done during the surgery, that is, ABT only or SBT with or with no ABT or NBT, the patient will be categorized into the appropriate study cohort. All patients undergoing MSTS will receive tranexamic acid as an intravenous bolus before induction of anesthesia as per the department protocol, with subsequent top-up dosages every 4 hours during MSTS. If excessive blood loss is expected during surgery, such as in a separation surgery, continuous infusion of tranexamic acid is given to the patient.

Postoperatively, all subjects will be followed up individually by their operating surgeons, as per the standard of care at the National University Hospital. No additional patient follow-up sessions by the research team will be required. Clinical data and patient outcomes will be accessed via the computerized patient support system and EPIC system at monthly intervals. All available radiological data and clinical notes from the patients’ follow-up by their treating surgeons or physicians will be reviewed by the research team. This is to determine the postoperative outcomes such as survival and disease progression. The collected data will be analyzed postoperatively at 3, 6, 12, 24, 36, and 48 months. The data collection and follow-up of available records will continue over a period of 4 years postoperatively or until the patient’s demise, whichever occurs first. The collected outcomes of the 2 experimental groups (patients who received SBT with or without ABT) will be compared with those of the control group (patients who received NBT) as well as with the available historical data from the literature.

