#### Analysis of Primary Outcome Measures

We intend to compare the proportion of patients with MSTS requiring blood transfusion and the amount of ABT required. The primary analysis will be based on the intention-to-treat principle. A Fisher exact test will be used to compare the 2 arms. The exact 95% CI will also be calculated for the difference in the ABT rate between the 2 arms.

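### The Abstract's Objective tests whether salvage reduces ABT among patients chosen because they need ABT, and the Methods form the groups by blood received, so the ABT comparison has no unselected denominator

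*Protocol article*

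**What the plan says.** Four parts of the protocol article bear on the ABT comparison.

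- **Abstract, Objective.** The ABT question is to be answered by "sorting patients undergoing MSTS who require ABT into patients who consent to receive or not receive SBT". This describes two groups, split by consent, among patients who need ABT.
- **Secondary Objectives.** The aim is to "investigate whether reinfusion of IOCS-LDF–processed blood can reduce ABT rates in patients undergoing MSTS", with no restriction to patients who need ABT.
- **Analysis of Primary Outcome Measures.** "We intend to compare the proportion of patients with MSTS requiring blood transfusion and the amount of ABT required". The analysis is by intention to treat, with a Fisher exact test and an exact 95% CI for the difference in ABT rate between two arms. That section does not define the arms.
- **Recruitment.** The plan is for "a minimum of 90 patients of whom 30 will receive SBT (with or with no allogeneic blood), 30 will undergo ABT", and 30 with no blood transfusion (NBT). SBT and ABT are called the two experimental arms. Of SBT-only patients it says "there are likely to be very few patients who receive only SBT", and it adds: "We will compare the number of patients receiving only SBT with those receiving ABT, if the sample sizes are sufficient". Cohorts are assigned from the anesthetists' transfusion details after the operation: "ABT only or SBT with or with no ABT or NBT, the patient will be categorized into the appropriate study cohort".

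**The concern.** A comparison of ABT rates needs a denominator in which a patient may or may not receive ABT. The Objective takes its denominator from patients who need ABT, so a patient for whom salvaged blood was enough falls outside it. The rate cannot differ between the groups, and the amount of ABT is compared only among patients who still needed some.

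The Objective matters beyond its place in an abstract. It is the only text that describes a two-group, consent-based split, and such a split is what an intention-to-treat analysis of two arms would need. A reader who looks for the arms of the primary analysis has two candidates: the Objective's groups, or the SBT and ABT cohorts of Recruitment. Both are selected on the outcome, in different ways. The article labels this comparison the primary outcome analysis.

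**Working it through.** **Inputs.** Cohort sizes of 30, 30 and 30 are from Recruitment (3 × 30 = 90, which agrees with the stated minimum). The Fisher exact test and the two-sided 5% level are from the statistical sections. The article gives no expected ABT rates or effect size, so there is no planned figure for this comparison to reproduce.

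**1. The Objective as written.** All patients in both groups have ABT. With 30 per group for illustration, this is 30/30 versus 30/30: difference 0, Fisher p = 1.0. The result does not depend on any model or on what salvage does.

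**2. The cohorts of Recruitment.** SBT-only patients stay in the SBT cohort. The ABT cohort is defined by having received ABT, so it is 30/30 by construction. When all k patients without ABT are in the SBT cohort, the two-sided Fisher p = 2 × C(30,k)/C(60,k).

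| SBT cohort with ABT | ABT cohort | p |
|---|---|---|
| 26/30 (k = 4) | 30/30 | 0.112 |
| 25/30 (k = 5) | 30/30 | 2 × 142,506/5,461,512 = 0.052 |
| 24/30 (k = 6) | 30/30 | 2 × 593,775/50,063,860 = 0.024 |

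If the ABT probability in the SBT cohort is assumed to be 0.90, 0.80 or 0.70, the chance of p < 0.05 is 0.07, 0.57 or 0.92. None of this requires salvage to spare anyone ABT. Take a patient who bleeds little and would not have been given allogeneic blood in any case. With salvaged blood that patient enters the SBT cohort as a non-ABT patient. Without it the patient enters NBT, never the ABT cohort.

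**3. What the Objective's restriction would hide (illustration only).** Assume ABT units per patient are Poisson with mean 3 without salvage. Background gives an average of 3 units for thoracic and lumbar decompression and instrumentation, and the distribution is my assumption. The rate in all patients is 1 − exp(−m). The mean among those with at least one unit is m/(1 − exp(−m)).

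- m = 3: rate 0.950, conditional mean 3/0.950 = 3.16.
- m = 1.5: rate 0.777, conditional mean 1.5/0.777 = 1.93.

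| True cut in mean units | Rate difference, all patients | Rate difference, ABT-requiring only | Fall in mean units, ABT-requiring only |
|---|---|---|---|
| 33% (m = 2) | 9 points | 0 | 27% |
| 50% (m = 1.5) | 17 points | 0 | 39% |
| 67% (m = 1) | 32 points | 0 | 50% |

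**4. An unselected denominator.** Assume 45 consenting and 45 non-consenting patients, all kept in. ABT rates of 60% versus 40% then give Fisher power 0.38, 60% versus 30% give 0.76, and 60% versus 60% reject in 0.03. The split and the rates are assumptions. The point is that the rate can now vary in both groups.

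**The case against.** The strongest reply is that one loose clause in a condensed abstract is not an analysis rule. The same sentence first names ABT rates in patients undergoing MSTS, no Methods section repeats the restriction, and consent is taken before surgery. On that view, needing ABT may mean being expected to need transfusion, judged preoperatively, which would be a harmless entry condition.

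Part of this stands. A reader might infer that every patient whom salvage spares from ABT is lost throughout the plan. The documents do not support that: Recruitment places SBT-only patients in the SBT cohort and plans a comparison for them if numbers allow. Nor do they show that the primary analysis will apply the Objective's restriction. The Poisson table illustrates the literal wording only. Its 95% ABT rate without salvage also sits awkwardly with a planned NBT cohort of 30 in 90.

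The rest does not rescue the comparison. Nothing in the article says that the need is judged before surgery. If the phrase means needing some transfusion, a patient who does not receive SBT can only be given ABT, so the comparator is again 100%. Falling back on the Methods leads to the cohorts by blood received, which have the same fault on one side and do not fit an intention-to-treat analysis.

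**Conclusion.** The point holds as an inconsistency that leaves the ABT comparison without a usable denominator. The Objective, as written, fixes the ABT rate at 100% in both groups and the difference at 0. It conflicts with Secondary Objectives and Analysis of Primary Outcome Measures on the population, and with Recruitment on how groups are formed. Recruitment does not repair it: the ABT cohort is 100% by construction, six SBT-only patients in 30 are enough for p = 0.024, and untransfused patients move to NBT.

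The 100% results and the Fisher p-values follow from the stated definitions and cohort sizes. The Poisson figures, the ABT probabilities and the 45/45 split are assumptions. The correction should be made, because the article calls this comparison the primary outcome analysis.

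**What to change.** 1. In the Abstract's Objective, delete the restriction to patients who require ABT.
2. In Analysis of Primary Outcome Measures, state that ABT rate and ABT amount are compared in all enrolled MSTS patients, grouped by consent to SBT recorded before surgery. SBT-only and untransfused patients stay in and count as no ABT and 0 units.
3. In Recruitment, state that the cohorts formed by blood received are not used for this comparison.

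**Cost.** The wording changes are small, and transfusion details are already collected after each operation. The real cost is the dependence on a preoperative record of consent to SBT. Ethical Considerations says that consent to the study and to receiving SBT is obtained from each patient before recruitment, which leaves unclear whether patients who declined SBT were enrolled and their refusal recorded. The article reports 140 patients already recruited. If the record does not exist for them, report the ABT comparison as descriptive only. Grouping by consent removes the selection on the outcome but remains nonrandomized, so differences between consenting and declining patients still need adjustment or caution.

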**Methods:**

We aim to recruit a minimum of 90 patients—30 patients for SBT, 30 patients for ABT, and 30 patients with no blood transfusion. SBT and ABT form the 2 experimental arms, whereas no blood transfusion forms the control cohort. Available patient data will be reviewed to determine tumor burden secondary to metastasis and postoperative survival and disease progression, improvement in pain, and neurological and ambulatory status. Data collected will be studied postoperatively at 3, 6, 12, 24, 36, and 48 months or until demise, whichever occurs first. Outcomes of the experimental groups will be compared with those of the control group. Outcomes will be analyzed using 1-way ANOVA and Fisher exact test. The Kaplan-Meier curve and a log-rank test will be used to study overall survival. A multivariate and competing risk analysis will be used to study the association between blood transfusion type and tumor progression. All statistical analyses will be done using Stata Special Edition 14.0 (StataCorp LP).

**Results:**

This is the largest clinical study on use of IOCS in MSTS from various primary malignancies to date. It will provide significant clinical evidence regarding the safety and applicability of IOCS in MSTS. It will help reduce use of ABT, improving overall blood management of patients undergoing MSTS. A limitation of this study is that not all patients undergoing MSTS will survive for the follow-up period (4 years), theoretically leading to underreporting of disease progression. Study commenced in 2016 and patient recruitment continued till 2019. As of September 2019, we have collected operative data on 140 patients. However, the 2-year outcomes of about 40.0% (56/140) of patients are in the process of collection. The study is aimed to be published in the years 2023-2024.

**Conclusions:**

Results will be disseminated via peer-reviewed publications, paving the way for future studies.

**International Registered Report Identifier (IRRID):**

DERR1-10.2196/54609

## Introduction

### Background

The skeletal system is the third most common site of metastases, and cadaveric studies show that spinal metastases can be found in 30% to 90% of patients who die of cancer [1,2]. Surgery for metastatic spine disease (MSD) is complex, often requiring wide resection and extensive reconstruction leading to significant blood loss [1,2]. Emergency surgical treatment is often indicated for spinal cord compression with actual or impending paralysis or for spinal instability with severe pain that reduces the quality of life and mobility [3].

Typical blood loss in a patient undergoing tumor decompression and instrumentation in the thoracic and lumbar spine is about 1500 mL, and this requires an average of 3 units of packed red blood cells [4,5]. This blood loss is currently replenished by allogeneic blood transfusion (ABT) across the world, placing a significant burden on the already limited blood bank resources [6,7]. On the contrary, there is increasing evidence of the deleterious effects of ABT. Many studies have shown an increased incidence of postoperative infections [8] and promotion of tumor growth [8,9], which is thought to occur secondary to immunosuppression and other transfusion reactions.

Despite evidence describing multiple postoperative complications related to ABT [10,11], it remains to be the mainstay of blood replenishment in patients with heavy intraoperative blood loss [12]. These are immune-mediated complications and commonly affect the lungs (eg, transfusion-related acute lung injury) [13,14], wound healing [15-17], and survival duration [11,16]. This has prompted efforts to decrease reliance on ABT and to increase the utilization of alternatives, such as autologous predonation or intraoperative cell salvage (IOCS). Autologous predonation may not always be possible in metastatic spine tumor surgery (MSTS) because of suboptimal patient status, medical comorbidities, and in cases where emergency surgery is indicated.

Patient blood management is an evidence-based, patient-tailored approach aimed at reducing the need for ABT and its associated risks [18]. Patient blood management has both preoperative and perioperative components. Preoperative techniques include patient optimization via cessation of antiplatelet and anticoagulant medications [19,20] and anemia management [18]. Perioperative management comprises achieving surgical hemostasis, reinfusion of intraoperatively salvaged blood, the use of erythropoietic agents, and hemostatic drugs such as tranexamic acid. Randomized [21,22] and nonrandomized [23] studies on the use of IOCS in nononcological surgical procedures indicate that salvaged blood transfusion (SBT) significantly reduces the need for ABT [21-23]. Despite extensive use of SBT in orthopedic, trauma, and cardiac surgical procedures [24], the concern of reinfusion of tumor cells leading to disease progression persists [25-27]. The initial lack of literary evidence on the safety of SBT in oncological surgical procedures has made oncological surgeons reluctant to use SBT in MSTS [25-27].

This reluctance dates to an American Medical Council report from 1986, which stated that SBT was not suitable for use in tumor surgery [28]. This was in turn based on a case report from 1975 where tumor cells were found in salvaged blood [29]. There were concerns that tumor manipulation and resection would result in the spillage of tumor cells into the surgical field [30], which would lead to further metastasis if reinfused via SBT. Recent evidence indicates that circulating tumor cells (CTCs), which are shed by the primary tumor [31], are the most likely cause of tumor metastasis in oncological patients. CTCs have been shown to be eliminated by the reticular endothelial system [32], once they fail to metastasize (unable to complete the process of metastasis). Other CTCs may undergo cellular apoptosis after being retained in the capillary bed or the bone marrow [32]. These host defense mechanisms can prevent metastasis by reducing the metastatic ability of the vast majority of CTCs [33]. Consequently, one can ask, “Can SBT with a limited load of damaged malignant tumor cells cause tumor metastasis and disease progression?”

Investigation on the use of salvaged blood in MSTS started with a systematic review that we published [34]. It was envisaged that there is a place for salvaged blood in MSTS, provided the safety of IOCS in MSTS is established by the following steps. Our first step was to establish *basic cellular evidence* that there are no viable tumor cells in the salvaged blood. Second, we aimed to *quantify the number of tumor cells in the salvaged blood*, if any, and to demonstrate that the CTCs in the patient’s own blood are far more than those present in the salvaged blood. Our proposed *final phase* of study was to provide *clinical evidence* that SBT is safe for use in oncological surgical procedures, without increasing the risk of disease progression or tumor recurrence or resulting in poorer prognosis [32].

Our working hypothesis for the preclinical phase of this study was that the blood salvaged from patients undergoing MSTS does not contain viable tumor cells, and even if it did, viable tumor cells in the salvaged blood would be significantly lower than the number of CTCs present in the patient’s own blood at any given point in time. Therefore, there should be no increase in the risk of disease progression, in terms of further tumor dissemination, decreased survival, or increased tumor recurrence.

To test this hypothesis, we first conducted a study that analyzed the morphology and structural integrity of the tumor cells present in the patient’s circulation, operative field, and pre- and postfiltration samples of the salvaged blood [24,35]. Using the cell block technique, salvaged blood in the pre- and postfiltration samples was shown to mostly comprise cytoplasmic debris with no viable nuclei [24,25], thereby establishing the safety of IOCS in oncological surgery [36]. This is also supported by evidence from other studies [37] stating that upon passing through the IOCS system, 62% of tumor cells were destroyed, whereas the remaining 38% were morphologically altered.

Using flow cytometric studies, we then compared the number of CTCs present in the patient’s own blood with that in salvaged blood [38]. We found that salvaged blood contained a significantly lower number of CTCs than those present in the patient’s circulation [38]. Furthermore, we provided corroborative evidence that tumor cells passing through IOCS become nonviable and therefore cannot form new metastatic lesions [36]. We were able to demonstrate that CTCs lost the ability to develop into new metastatic lesions after passing through the IOCS apparatus, even without the use of leukocyte depletion filters (LDFs) [36]. LDFs are used to prevent leukocyte-mediated adverse reactions and have applications in both transplant surgery and treatment of hematological conditions [39]. LDFs are used for filtrating blood and have been proven to have the capability to remove tumor cells from the filtrate [38].

Currently, there is ample evidence in the literature for the clinical safety of salvaged blood used in oncological surgical procedures, including gastrointestinal [40], gynecological [41-43], hepatobiliary [40,44-46], and urological [47-54] surgical procedures (Multimedia Appendix 1 [55-64]). Although patients who received SBT required significantly lower amounts of allogeneic blood, their survival rates [44,49,51,52] and disease progression remained comparable with those who did not receive SBT [42,46,54,65]. Patients who received SBT had lower or similar rates of recurrence compared with the control cohort [47,49,51,53].

Despite the validity of the abovementioned literature, there still is hesitation to use IOCS in MSTS [34]. This can be addressed only by using a clinical study. Hence, we have designed this study to analyze the clinical use of IOCS in patients undergoing MSTS.

